#### *Repertoire analysis*

Intestinal biopsies taken from children at partner site 1 will require no transport and can be analyzed directly. Biopsies taken at sites different from that of partner 1, will require transportation before the culturing of gluten reactive T cells. It is uncertain how well biopsies will maintain their ability to produce functional T cell reagents. This will be tested in simulation experiments before large scale transfer of biopsies will take place. In these simulation experiments we will define the best conditions for transport. If transportation of biopsies does affect T cell outgrowth, we will develop alternative protocols through which the start of the biopsy cultures can be initiated at sites other than partner 1 and 13. Such sites could include partners 2, 4, 6 and 7. After the initial outgrowth of the T cells these could be frozen and shipped to partners 1 and 13 for further analysis.

#### *Regulatory T cell compartment*

There is now a large body of literature of markers through which regulatory T cell can be identified through FACS-analysis. Markers include Fox-p3, CTLA-4, CD4CD25 and characteristic cytokine secretion profiles. The techniques for this analysis are all well established. We therefore see no risks associated with this part of the work package.

WP7: no contingencies or risks are expected in this WP.

## 6. Project management and exploitation/dissemination plans

The management and governance structure of PREVENTCD ensures:

- Effective and optimised management;
- Effective and optimised decision making;
- Enhanced networking between the participants and stakeholders (like patient organisations, public health authorities, research initiatives on coeliac disease (CD)).

The public participation and awareness of the project will be raised by widely dissemination of its activities and results to other directly interested parts, such as food industry, CD patients and patients associations.

The PREVENTCD project will have a *website* and a *newsletter* both to facilitate internal communication, and to make the process and results easily accessible externally. Once strategies for primary prevention of CD have been identified the new European platform on CD formed by EU funded project CDEUSSA (Food – CT-2005- 517787) will contribute to the promptly *dissemination of the new findings to reach and be of benefit to the European citizens health and well-being*. The results will be reported at *national and international scientific meetings*, and published in *national and high impact international journals*. The European citizen, the CD patients and their families, the CD patients Societies, the Food Industry and other relevant groups will be reached by the knowledge gained through workshops and by information on flyers and on-line publications.

### 6.1 Project management

PREVENTCD is an organization of 14 research, health care, industry and patients' associations with a vested interest in life sciences research, especially in the field of CD. The relationships between the 14 partners in PREVENTCD and their rights and obligations with respect to each other and the project will be regulated in the **Consortium Agreement** for the project according to the STREP requirements. These agreements will be signed before the actual start of the project. The management and governance structure are shown in figure 1.

[figure not shown]

Figure 1. Management and governance structure of PREVENTCD

The **coordinator, [name]**, of the Leiden University Medical Center (LUMC), acts as the coordinator of PREVENTCD and is responsible for the project reporting and accounting. The duties of the coordinator are described in the Consortium Agreement. They include administrative and financial management, legal and contractual issues, organization of meetings, creating and maintaining the website, and functioning as the central contact and communication point for the European Commission. A **Project Assistant** will support the co-ordinator in her tasks. She/he will be responsible for setting up the **Project Office**, for management, financial accounting and organizational aspects, and for maintaining the web-based activities and the networking activities. They will receive assistance within the LUMC from a financial project officer, an officer of European research grants, from IPR and legal experts, and from ICT specialists and communication experts.

The coordinator will ensure that reports are prepared and submitted to the EC project officer in time and according to instructions (i.e. periodic- mid-term- and final reports, including cost statements and audit certificates).

The **Project Council**, which is composed by the representatives from all the collaborating organisations and is chaired by the co-ordinator, is responsible among others for:

1. Deciding upon the allocation of the project's budget in accordance with the EU Contract, and reviewing and proposing budget re-allocations;
2. Deciding on the plan for using and disseminating knowledge arising from the project.

The major decision making body in the PREVENTCD project is the **Management Team**, which is composed by the leaders of the 7 Work Packages and is chaired by the coordinator. The PREVENTCD **Management Team** will be responsible for the day-to day direction of the project and will be responsible, among others for:

1. Deciding upon changes to the roadmap of activities necessary to achieve the objectives of the project;
2. Deciding upon measures in the framework of controls and audit procedures to ensure effective day-to day coordination and monitoring of the work affecting the project.

The PREVENTCD **Management Team** will meet quarterly. The coordinator and the Management Team together constitute the PREVENTCD management. In order to assist in the management tasks, the website of PREVENTCD will contain a Project Management System.

An **Advisory Board** will be formed by the experts of the European platform on CD, created by the EU SSA project CDEUSSA (Food – CT- 2005- 517787). A list with the members of the CDEUSSA European platform of experts on CD is included in annex 10.2. The aim of this platform of experts is to close the gap between basic science on CD and applications of its results in prevention, clinical treatment and in the food industry. The CDEUSSA platform on CD is formed through European collaboration among leaders from disciplines beyond those traditionally used; among others from academia, patients' associations and industry, so, as to generate a

scientific basis for innovative research on primary prevention and effective treatment of CD. Members of the Management Team will present the results of the project during the platform meetings and will receive advice from the platform on scientific and industrial aspects and with regard to the patients' interest.

### **Ethical management**

Because of the potential ethical aspects of the project the management structure will include as ethical advisor [name], chairman of the Helsinki Committee at Rambam Medical Center and member of the Steering Committee of the Israeli Ministry of Health for Regulatory Issues and Monitoring of Clinical Trials in Human Subjects (annex 10.3 CV). The ethical advisor will give advice, asked and unasked, to the Management team of the project with respect to the ethical questions and decisions. See Ethical review PREVENTCD (annex 10.4).

### **Planning and Control**

PREVENTCD is a project in which decisions on activities to be undertaken will be made centrally. On the other hand, the execution of these activities will be decentralized. The activities are subdivided in 7 **Work Packages**. For each Work Package one of the partners is made responsible. The responsible partner or **Work Package Leader** coordinates a taskforce designated to achieve the goals set out in the Work Package description. The overall planning of the PREVENTCD project is given in part 7 (Workplan) and in the Gantt charts. For the planning the following procedure will be followed. Every three months, progress will be reported at the Management Team meetings. In case of changes in planning or research, the Work Package Leaders will propose measures needed to realise the Project's goals. The management will decide minor changes in the execution of the project. The Project Consortium will decide on major changes. However, it is expected that there will be no large deviations from the overall work plan submitted in this proposal.

Every three months the Management Team will make an evaluation of the progress of the project based on material that has been submitted to the project database and on short progress reports submitted to the coordinator. These reports should at least contain descriptions of the deliverables and milestones achieved and a self-evaluation of the progress and difficulties encountered. Because of the close coupling of planning and control within a three months cycle, the Management Team will be able to control

the project closely and to adjust the various building blocks where needed, or shift activities between partners.

### **Role of the Partners**

Each partner forms part of a larger network of related institutes and research centres in Europe and has a track record in performing and coordinating large nationally projects, funded on a national or European level. A partner will participate in several other Work Packages as described in the work plan (part 7). Each partner has the right to re-allocate resources in the Work Package, subject to the prior permission of the management, the Project Council and the EC representative. Adjustments in the Work Package resulting in other and/or delayed milestones and deliverables require prior permission of the Management Team.

### **Communication**

The communication in the PREVENTCD project will first of all be based on the Internet. A website will be maintained in which all information is brought together. This information is accessible to the partners and to the research community at large whenever appropriate. An area with restricted access will be used for communication on:

1. Management issued and storage of used documents (i.e. reporting formats);
2. Research data, results and discussions (see WP 7).

Twice a year **progress meetings** will be organized in which all the partners are expected to participate. These progress meetings will also have a formal role in the management of the project, because at these meetings the progress report will be presented and decisions will be made with respect to the plans for the next period. The partners will be obliged to submit their contributions for this report in time. Other means of communication, like e-mail, telephone calls or telephone conferences, will also be used when useful or necessary to fulfil the obligations of the project.

### **Intellectual Property Rights and Exploitation**

The PREVENTCD partnership functions as an European Interest Group in the sense that the partners strive to realise joint objectives in order to establish scientific bases for effective prevention of the most common food sensitivity in Europe (CD). There may be a need to explore the role of intellectual property rights (IPR) protection for

research results derived from the project. The partners are members of larger research organizations and universities which have gained considerable experience in protecting IPR and in the exploitation of knowledge. It should not be difficult to involve experts from within the partners' institutes. The results of PREVENTCD will be scanned (yearly and before publication of results) for IPR potential by the IPR specialists employed by the participants. The involvement of three industrial companies and patient organisations ensures that results will be implemented and commercialized in (baby) food and diagnostics. Through national networks several participants have contacts with other industrial stakeholders. These will be contacted if the use of results is foreseen in other areas than the present industrial participants are working. IPR issues will be arranged in a Consortium Agreement.

## **6.2 Plan for using and disseminating knowledge**

The results of PREVENTCD will be disseminated beyond the consortium as described in WP7. Stakeholders and users are public health professionals, patients (through patients' associations), researchers, regulatory bodies, governments, and the European Commission. These will be reached by a mix of communication measures like the website, newsletters, presentation at conferences and meetings, publications in journals, and new guidelines. The targeted dissemination ensures exploitation/use of the results in the public health sector.

The results of PREVENTCD will, if appropriate, take the form of policy statements on a European Common Strategy to prevent CD. PREVENTCD will offer new, evidence-based, European Guidelines for early feeding practices, including gluten exposure and breast-feeding. Such results will be presented to the scientific community as a position paper and to the coeliac patients and the Europeans in general in the form of flyers and on-line publications. Regulations, rights and obligations with respect to prior knowledge (prior defined as preceding the date of contract signature) will adhere to standard regulations defined in the model contract.

## **6.3 Raising public participation and awareness**

The results of the project will be widely disseminated to other directly interested parts, such as food the industry and patients' associations. Once the strategies for primary prevention of CD will have been identified, the ongoing integrated research

collaboration network will facilitate the dissemination of the new findings, in that it promptly will reach and be of benefit to the European citizens' health and well-being.

## **7. Workplan– for whole duration of the project**

### **7.1 Introduction - general description and milestones**

*Our hypothesis is that early dietary history, i.e. the introduction of small quantities of gluten during the period of breast-feeding, may prevent coeliac disease (CD) in genetically predisposed individuals by induction of tolerance for gluten and for other related auto-antigens.*

Through integration of novel collaborative research among European leaders from different and crosscutting areas we will examine the complex interactions and molecular mechanisms involved in the development of CD including:

1. Genetic background: stratification by genetic risk in the individual and the family;
2. Early immune response to gluten introduction;
3. Early dietary history including:
  - c. Gluten introduction and
  - d. Breast-feeding

*To identify safe strategies for primary prevention of CD in genetically predisposed children.*

Our strategy will include a roadmap for the integration of nutrition intervention studies, both in a cohort of children with a high-risk for developing CD as in the general population, with genetic and immunology response trials where the early dietary history in relation to the development of CD is considered.

The project will be achieved by collaboration of European crucial players in the field of CD, not only in the basic scientific community, but also in clinical practice, food industry, Public Health and patient organizations, determined to pro-actively cooperate on an integrated European research project on effective prevention of CD. Our project represents an example of Transitional Medicine aiming to integrate the knowledge from basic science into clinical applications providing solutions to the problems of the Europeans suffering from CD.

#### **To achieve our objectives we propose the following structure and methodology:**

1. A prospective early dietary intervention study in 1000 young children from high-risk families for CD with at least one case of CD among the siblings and

/or the parents, to assess the possibilities to induce immune tolerance for gluten in genetically predisposed children;

2. A prospective dietary intervention population study in 16.000 Swedish children aged 12 years, born during and after the Swedish epidemic of CD, to assess the late effect of dietary history, concerning gluten exposure and breast-feeding, on the development of CD and related autoimmune phenomena.

The work of the proposed STREP will be integrated in the following Work Packages (WP):

- WP 1. Management
- WP 2. Start-up phase
- WP 3. Family study: European early feeding intervention study in infants from high risk families for CD
- WP 4. Population based study exploring birth cohorts with different early dietary history
- WP 5. Genetics
- WP 6. Immunological studies on early response to gluten introduction
- WP 7. Dissemination

## 7.2 Workplanning and timetable

The work planning of the project, showing the timing of the different Work Packages (WP's) and their components is presented in figure 2 (Gantt chart).

| Months project |     |   |   |    |     |    |    |    |     |    |    |    |     |    |    |    |     |    |    |    |
|----------------|-----|---|---|----|-----|----|----|----|-----|----|----|----|-----|----|----|----|-----|----|----|----|
| Y              | 1st |   |   |    | 2nd |    |    |    | 3rd |    |    |    | 4th |    |    |    | 5th |    |    |    |
| WP             | 3   | 6 | 9 | 12 | 15  | 18 | 21 | 24 | 27  | 30 | 33 | 36 | 39  | 42 | 45 | 48 | 51  | 54 | 57 | 60 |
| 1              |     |   |   |    |     |    |    |    |     |    |    |    |     |    |    |    |     |    |    |    |
| 2              |     |   |   |    |     |    |    |    |     |    |    |    |     |    |    |    |     |    |    |    |
| 3              |     |   |   |    |     |    |    |    |     |    |    |    |     |    |    |    |     |    |    |    |
| 4              |     |   |   |    |     |    |    |    |     |    |    |    |     |    |    |    |     |    |    |    |
| 5              |     |   |   |    |     |    |    |    |     |    |    |    |     |    |    |    |     |    |    |    |
| 6              |     |   |   |    |     |    |    |    |     |    |    |    |     |    |    |    |     |    |    |    |
| 7              |     |   |   |    |     |    |    |    |     |    |    |    |     |    |    |    |     |    |    |    |

(Y= year of the project; WP = work package)

The proposed STREP requires duration of 5 years because:

1. The 1000 infants from the family study are enrolled during pregnancy, born during the period of the project and CD can be assessed at the age 2-3 years.
2. The time required to carry out the large population study in 2 cohorts of 8.000 children

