| D2.1                        | Digital standardized forms            | 2             | 1                       | 2                              | P                         | CO                                     | M 4                                               |
| D2.2                        | Digital databank for data management  | 2             | 1                       | 1                              | P                         | CO                                     | M 6                                               |

 Deliverable numbers in order of delivery dates: D1 – Dn

 Please indicate the nature of the deliverable using one of the following codes:

**R** = Report

**P** = Prototype

**D** = Demonstrator

**O** = Other

 Please indicate the dissemination level using one of the following codes:

**PU** = Public

**PP** = Restricted to other programme participants (including the Commission Services).

**RE** = Restricted to a group specified by the consortium (including the Commission Services).

**CO** = Confidential, only for members of the consortium (including the Commission Services).

 Month in which the deliverables will be available. Month 1 marking the start of the project, and all delivery dates being relative to this start date.

|      |                                                                                                                                                                                                    |   |   |     |   |    |                                         |
|------|----------------------------------------------------------------------------------------------------------------------------------------------------------------------------------------------------|---|---|-----|---|----|-----------------------------------------|
| D3.1 | European databank on the interaction between early gluten intake and breast-feeding in children from high-risk families for CD, their early immune response to gluten and their genetic background | 3 | 2 | 90  | P | CO | M 54                                    |
| D3.2 | Report on the possibilities to achieve primary prevention for CD in genetically predisposed children by early dietary history intervention                                                         | 3 | 2 | 5   | R | CO | M 56                                    |

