| Months                             | Pregnancy | Birth | 1 | 2 | 3 | 4 | 5 | 6 | 7 | 8 | 9 | 10 | 11 | 12 | 14 | 16 | 18 | 20 | 22 | 24 | 28 | 30 | 34 | 36 | 48 |  |
|------------------------------------|-----------|-------|---|---|---|---|---|---|---|---|---|----|----|----|----|----|----|----|----|----|----|----|----|----|----|--|
| Enrolment                          | +         |       |   |   |   |   |   |   |   |   |   |    |    |    |    |    |    |    |    |    |    |    |    |    |    |  |
| Randomisation                      |           |       |   |   | + |   |   |   |   |   |   |    |    |    |    |    |    |    |    |    |    |    |    |    |    |  |
| Intervention                       |           |       |   |   |   | + |   |   |   |   |   |    |    |    |    |    |    |    |    |    |    |    |    |    |    |  |
| Anthropometrics                    |           | +     | + | + | + | + | + | + |   |   | + |    |    | +  |    |    | +  |    |    | +  |    |    |    | +  | +  |  |
| Clinical History                   |           | +     | + | + | + | + | + | + | + | + | + | +  | +  | +  | +  | +  | +  | +  | +  | +  | +  | +  | +  | +  | +  |  |
| Food Questionnaire                 |           | +     | + | + | + | + | + | + | + | + | + | +  | +  | +  | +  | +  | +  | +  | +  | +  | +  | +  | +  | +  |    |  |
| Cord blood Sample Genetic study    |           | +     |   |   |   |   |   |   |   |   |   |    |    |    |    |    |    |    |    |    |    |    |    |    |    |  |
| Breast milk Sample                 |           |       | + | + | + | + | + | + |   |   | + |    |    |    |    |    |    |    |    |    |    |    |    |    |    |  |
| Blood sample Immunological Studies |           |       |   |   |   | + |   | + |   |   | + |    |    | +  |    |    | +  |    |    | +  |    |    |    | +  | +  |  |

- Follow-up 0-4 years: All the children will be frequently controlled for clinical and nutritional assessment and for the presence of immunological markers of gluten (in)tolerance, including determination of serum IgA antibodies against gliadin and tissue trans- glutaminase (tTGA) (table 1). In case of health complaints extra controls will take place and, if indicated, the intervention will be stopped.

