- Diagnosis of CD: The parents of the children with tTGA or symptoms of CD will be offered a small bowel biopsy for the diagnosis of CD. Biopsie will only be performed when medically indicated, that is: only in these children with CD antibodies in their serum that indicate gluten sensitivity and are highly suspect for active CD, and NOT just for purpose of the study. Such children would undergo a biopsy also in non-study circumstances.

A reduction of 50% of CD among the intervention group at the age of 3 will be considered as an effective prevention.
- Power Analysis:(80%, significance level 5%, 2-sided test): Assuming a frequency of 10% CD among the enrolled infants we need to study 474 children randomized to tolerance induction and 474 controls. The number of members of the participating Coeliac Disease Societies (table 3) makes the study feasible.

Table 2. Members of the coeliac disease patient societies collaborating in the project

| CD Societies | Members
(no.) | 0-10 years
(siblings)
(no.) | Female
Fertile age
(mothers) (no) | Male
Fertile age
(fathers) (no.) | Expected newborns to be
recruited
(no.) |
|--------------|------------------|-----------------------------------|-----------------------------------------|----------------------------------------|-----------------------------------------------|
| Netherlands  | 7902             | 1494                              | 670                                     | 390                                    | 150                                           |
| Campania     | 3000             | 800                               | 300                                     | 100                                    | 150                                           |
| Madrid       | 5133             | 2413                              | 387                                     | 162                                    | 100                                           |
| Valencia     | 2050             | 475                               | 152                                     | 67                                     | 75                                            |
| Israel       | 4800             | 800                               | 470                                     | 830                                    | 100                                           |

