NIZO will pay special attention to the microbiological assessment of the products and will make sure that the results will be in accordance with the standards of Danone. Also it will be analytically verified whether the blending of the materials has been adequate and resulted into a homogeneous mixture. Compliance will be assessed by visit or interview.
- After the 8 weeks intervention period, all the families will be advised to gradually introduce gluten into the diet of their children, and to increase it gradually till the age of 12 months, for which simple recommendations will be provided to the parents.
- The infants will be strictly followed up (Table 1). Blood (5 ml) is sufficient to allow for the screening of CD-specific antibodies, phenotypic characterization of 20 markers indicating lymphocyte activation and regulatory T cell induction, and monitoring for the occurrence of gluten-specific T cell responses typical for CD. At age 3 years 10 ml blood will be obtained to test for additional (auto)immune phenomena related to the development of CD.
- Children with positive antibodies strongly indicating CD or with clinical suspicion of CD will be offered a small bowel biopsy for the definitive diagnosis a reduction of 50% of CD among the intervention group at the age of 3 will be considered as an effective prevention.

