### **Deliverables**

- D.3.1 European databank on the complex interaction between early gluten intake and breast-feeding in children from high-risk families for CD, their early immune response to gluten and to other related auto-antigens and their genetic background (m 44)
- D.3.2 Assessment of the possibilities to achieve primary prevention for CD in genetically predisposed children by early dietary history intervention (m 46)
- D.3.3 New European guidelines for early nutrition, concerning gluten introduction and breast-feeding (m 48)
- D.3.4 350 newborns enrolled (m12)
- D.3.5 700 newborns enrolled (m 24)
- D.3.6 1000 newborns enrolled (m 36)

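### Success and power are set on CD at age 3, but about 42% of the planned children would be under 3 when the efficacy report is due at month 56, and 30% when the guidelines are due at month 60

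*Protocol*

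**What the plan says.** The success criterion is in the WP3 Introduction of the Protocol (section 7.6): "A reduction of 50% of CD among the intervention group at the age of 3 will be considered as an effective prevention". The WP3 Description of work repeats it. The power statement follows directly: 80% power, two-sided 5%, 10% CD, 474 children per arm.

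The enrolment deliverables are 350 newborns at month 12, 700 at month 24 and, last, "D.3.6 1000 newborns enrolled (m 36"). Section 7.5 gives the same three dates.

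The efficacy deliverable D3.2 has two dates. Section 7.5 lists it as "Report on the possibilities to achieve primary prevention for CD in genetically predisposed children by early dietary history intervention", due M 56. The WP3 deliverables list reads "D.3.2 Assessment of the possibilities to achieve primary prevention for CD in genetically predisposed children by early dietary history intervention (m 46"). The guidelines D3.3 are due at M60 in section 7.5 and at m48 in WP3. The public guidelines (D7.6) and milestone M8 are due at M60, when the project ends.

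Section 7.2 explains the length of the project ("The proposed STREP requires duration of 5 years because") by noting that the infants are "born during the period of the project and CD can be assessed at the age 2-3 years". The WP3 assessment schedule runs to 48 months under "Follow-up 0-4 years".

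The Protocol does not say how children under 3 at the read-out are to be counted.

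**The concern.** A frequency of CD at age 3 is fully observed only in children who have had their third birthday. A newborn enrolled at month 36 is 20 months old at M56 and 24 months old at M60. The stated 80% power assumes 474 children per arm with a known age-3 status, and that number is not available at either date.

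If the report drops the younger children, the comparison is underpowered. If it keeps them and counts those without a diagnosis as free of CD, it understates the risk in both arms. European feeding guidelines are to be written on this result, so the reader needs to know whether the M56 and M60 outputs are final or interim.

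**Working it through.** **1. The plan's own sample size.** Inputs from the WP3 Introduction: p1 = 0.10, p2 = 0.05 (a 50% reduction), two-sided 5%, 80% power. Let d = 0.05 and mean proportion = 0.075.

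- Uncorrected: n = (1.960 × √(2 × 0.075 × 0.925) + 0.842 × √(0.10 × 0.90 + 0.05 × 0.95))² / d² = (1.960 × 0.3725 + 0.842 × 0.3708)² / 0.0025 = 434.4, so 435 per arm.
- Continuity-corrected: n/4 × [1 + √(1 + 4/(n × d))]² = 473.6, so 474 per arm.

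The stated 474 reproduces exactly, so the plan is powered for 10% against 5%.

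**2. Who has turned 3.** A child is 36 months old at read-out R only if born by month R − 36. Enrolment month is taken as birth month, because the deliverables count newborns.

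| Read-out | Born by | Aged 3 or more, of 1000 | Under 3 |
|---|---|---|---|
| M56 | month 20 | 350 + 350 × 8/12 = 583 | 41.7% |
| M60 | month 24 | 700 | 30% |
| Month 72 | month 36 | 1000 | 0% |

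The M60 row uses a milestone directly. The M56 row assumes even accrual between months 12 and 24. Without that assumption, the number born by month 20 lies between 350 and 700, so 30% to 65% are under 3 at M56.

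Section 7.2 says families are enrolled during pregnancy. If the milestones counted that moment, an assumed lag to birth of 3 or 6 months would raise the share under 3 to 50% or 59% at M56, and to 39% or 47.5% at M60.

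Only HLA-DQ2/DQ8 carriers are randomised. The shares do not change if carriers accrue in proportion.

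**3. Power if only children aged 3 are compared.** Power = Φ[(d√n − 1.960 × 0.3725) / 0.3708]; the continuity-corrected version replaces d by d − 1/n. The 1000 are split equally.

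| Cut | n per arm | Corrected | Uncorrected |
|---|---|---|---|
| M56 | 292 | 57% | 63% |
| M60 | 350 | 66% | 71% |
| Plan | 474 | 80% | 83% |

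**4. What partial follow-up recovers.** Simulation: 3000 trials of 948 children, births following the milestones, and a constant hazard from 9 to 36 months giving 10% and 5% by 36 months. That hazard is an assumption and is not in the Protocol. A log-rank test on all children, censored at the cut, has about 79% power at M56 and about 81% at M60. The age-3-only comparison has about 62% and 69%. At month 72 both have about 84%.

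**The case against.** Four points on the other side have weight.

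**The WP3 dates look superseded.** A reader might take m46 as the read-out, conclude that 71% of children are under 3, and put the power at 29-37%. The documents do not support that as the plan. The earlier WP3 dates belong to a pattern: D4.2 is month 42 in WP4 and M54 in section 7.5, D5.6 is m48 and M60, and D6.3 is m44 and M54. Milestone M7 carries m48 in its name beside a delivery date of M60, and WP3 itself presents its results at m60. The mismatch needs reconciling but should not set the size of the problem.

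**The Protocol prescribes no age-3-only analysis.** This stands. The power loss in step 3 belongs to one possible analysis. CD diagnosed before 3 already counts as CD by age 3, blood is drawn at 4, 6, 9, 12, 18, 24 and 36 months, and a censored analysis could recover most of the power. It would be wrong to say that younger children contribute nothing. The method may be left to the SAP. The endpoint age, accrual and report dates are fixed in the Protocol, and an SAP cannot make a child born at month 36 three years old by M60.

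**Section 7.2 does not redefine the endpoint.** This also stands. The sentence justifies the length of the project. It is loose beside the age-3 criterion, but it sets no rival endpoint.

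**Early reporting need not unblind families.** A reader might infer that it does. D3.2 is graded confidential to the consortium, and nothing says that individual allocations are released. Investigators belong to the consortium, so their masking is still worth protecting.

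**Conclusion.** The point holds in limited form. The 80% power stated for CD at age 3 is not available for that endpoint at the stated read-outs. With milestones met on time, about 42% of the 1000 children are under 3 at M56 (even accrual; 30% to 65% from the milestones alone) and 30% at M60. The last third birthday falls at about month 72. Restricting the comparison to children who have turned 3 gives 57-63% power at M56 and 66-71% at M60.

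The loss is not inevitable: censored follow-up brings power back to about 80% under the assumed constant hazard. The documents therefore do not support saying that the trial forfeits its power. They do support saying that the Protocol's dates and its endpoint do not fit, and that the status of the M56 and M60 outputs is undefined. This is a should-fix point.

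**What to change.** 1. Estimate the Kaplan-Meier cumulative incidence of CD to 36 months by arm in all randomised children, censored at the data cut, with a log-rank comparison. Keep cumulative incidence at age 3 as the estimand, because immature follow-up can credit a delay in onset as prevention. Onset is known only between visits, which are widely spaced after 24 months, so address the interval censoring.
2. State the power at the actual data cut, with the assumed timing of onset.
3. Label the M56 efficacy report and the M60 guidelines as interim until all randomised children have reached age 3. Add a final age-3 analysis from the follow-up already planned to 4 years, and keep individual allocation masked until then.
4. Use one set of dates for D3.1 to D3.3, and align the age wording in section 7.2 with the age-3 criterion.

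Items 1, 2 and 4 cost wording and a short calculation. Item 3 puts the confirmatory claim about a year after the project ends (month 72 against month 60), so the final analysis needs an owner and resources beyond month 60. Formally extending the whole project would be costlier and is not required by this point.
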